# 1. PROTOCOL SUMMARY

## **Trial Title and Protocol Number/Code**

*Trial Title:* Use of kinematic assessment of hand tremor pre- and post-treatment with botulinum toxin type A in essential tremor and Parkinson disease.

*Protocol Number:* 18445

## **Background and Rationale**

### *Botulinum Toxin A (BoNT A) and Essential Tremor (ET)*

Almost four decades since its introduction, BoNT A has become widely used in numerous medical and therapeutic applications, particularly for the treatment of hyperkinetic movement disorders such as tremor, tics, myoclonus, and spasticity [1, 2]. Tremor is one of the most common movement disorders; ET is a leading cause of neurology referral for clinical assessment of tremor [3]. Despite early doubts [4] and reported lack of benefit in tremor reduction [5], efficacy of BoNT A has been demonstrated for tremor of the hand [6,7], head [8,9], and even voice [10,11].

### *BoNT A and Idiopathic PD (IPD)*

Behind ET, IPD is the second most common cause of tremor. BoNT A therapy has been investigated for treatment of tremor in this population as well as in ET. While tremor is a benign symptom of IPD, it is frequently targeted for treatment as it often leads to social anxiety and inconvenience in daily living. Therefore, tremor has become an important indicator in clinical standard of care for IPD severity, progression, and medication inadequacy. The majority of studies reporting use of BoNT A therapy have studied ET patients [6,7,12], though a few studies have used IPD patients [13,14,15]. Therefore, there is a deficit in understanding of the effects of BoNT A therapy for IPD tremor, and the complete lack of literature regarding BoNT A therapy efficacy for different types of tremor. The present study aims to fill this knowledge gap by investigating the differential effect of Xeomin® on ET compared to IPD.

### *Advantages of BoNT A*

To date, efficacy in treatment of essential tremor by oral medication has been sub-optimal for all individuals. Propranolol and primidone are the most commonly prescribed medications, yet they have only limited efficacy for tremors of high amplitude, and often cause unpleasant side effects such as hypotension, as well as mood, behavioural, and cognitive impairment. In IPD, tremor is one of the least responsive symptoms to L-dopa therapy. Therefore, effective BoNT A therapy for treatment of tremor may be more effective at reducing tremor than the currently prescribed oral medications for either ET or IPD, and for IPD patients, could prevent unnecessary increases in L-dopa dosage. Management of tremor via local intramuscular injection of BoNT A introduces an optimal alternative to increasing medication prescription and dosage in ET [6,7,15] and IPD [15]. Collectively, these findings suggest that there is a substantial benefit in studying the efficacy of Xeomin® in tremor management in ET and IPD.

### *Kinematics*

While most studies of tremor treatment with BoNT A have used clinical rating scales to assess upper limb tremor, some have also used accelerometry as an objective kinematic measure of tremor severity [6,8,9,16]. Accelerometry, however, is limited not only in its ability to capture

and characterize tremor, but also in its ability to determine injection efficacy. Accelerometry measures the overall amplitude and frequency of tremor, but does not capture the contribution of individual muscle groups, is unable to measure the contribution of different joints (wrist, elbow, shoulder) to the tremor, and cannot be used to separate movement in different degrees of freedom (e.g. flexion/extension, radial/ulnar deviation and pronation/supination for the wrist). In the proposed study, we expand on previous studies by including a greater scope of kinematic measurements (using goniometers, inclinometers, and accelerometers) to increase our understanding of tremor and efficacy in the use of Xeomin® in tremor management.

#### *Kinematic Assessment vs. Clinical Assessment*

Preliminary work on kinematic recordings of tremor in ET and IPD indicates that upper limb tremor is comprised of a combination of complex movements and often involves components from different muscle groups at different joints (flexor/extensor, ulnar/radial deviators, and pronator/supinator for the wrist; flexors/extensors for the elbow and flexors/extensors and abductors/adductors for the shoulder). This finding supports the practice of injection individualization [6]. The biomechanics of upper limb tremor are multi-faceted and complicated; injection practice should reflect this complexity. It is likely not reflected by current gold-standard clinical assessments that rely on visual inspection alone, and may explain the inability of previous studies to demonstrate efficacy of BoNT A injection therapy for the treatment of tremor [5]. Improving injection accuracy by pinpointing sites of tremor origin and calculating appropriate dosage may be the key to achieving efficacy with BoNT A therapy. Kinematic biomechanical assessment tools may help to quantify, understand, and improve efficacy of injection practices. Presently, the objective decomposition of tremor into all components and the determination of injection parameters based on this data has not been adequately researched in the literature [17]. The present project attempts to fill this knowledge gap, allowing for the development of accurate and reliable kinematic recording methods, biomechanical analysis methods and consequently, development clinical expertise in tremor management using BoNT A injections.

## **Trial Objectives**

1. Investigate the efficacy of Xeomin® injections based on kinematic parameters in the treatment of upper limb tremor in Parkinson disease (IPD) and essential tremor (ET)
2. Assess the benefit of using kinematic measurement tools for determining BoNT A injection parameters
3. Study upper limb tremor composition in ET and PD patients using kinematic assessment

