## *Research questions:*

- i. Is there a significant improvement in tremor severity, as measured by standardized clinical assessment tools, post Xeomin® injection using kinematic guided injection parameters, for both IPD and ET patients?
- ii. Is there a significant reduction in overall tremor amplitude (as measured kinematically) post Xeomin® injection using kinematic guided injection parameters for both IPD and ET?
- iii. What is the difference in composition of tremor at baseline between two subgroups of participants: those with > 8 points change on the standard Fahn-Tolosa-Marin Tremor Rating Scale (FTM scale) and those with ≤ 8 points change the FTM scale?

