## **Study Design and Duration**

*Study Design:* open-label, pre-/post-treatment study design.

A pilot study design was selected to investigate the effect of this particular BoNT A formulation on both IPD and ET when kinematic data is used to determine injection parameters. A control group is difficult for this study given that it would not be appropriate to inject individuals without tremor. Additionally, at this stage of the study, with very little published literature on this BoNT-A formulation, completing a randomized study between two BoNT A formulations

would not be reasonable. Instead, we have chosen to expose all participants to the same treatment.

Seventy participants will complete six injection cycles over 96 weeks. Participants will be allocated to one of two groups IPD (35 participants) or ET (35 participants) following assessment by a Movement Disorders Neurologist (MDN). To optimize BoNT A therapy efficacy, adjustments to injection site and units injected will be made as required later in the study based on benefit observed from previous injection cycles. Clinically judged improvement (by the MDN) and patient reported improvement will be the determinants of need for dose/injection site modification. If the first injection was sufficient in reducing tremor to an acceptable level, the same injection will be repeated. If not, then the injection parameters will be modified by the MDN. Routine clinical use of BoNT-A for tremor usually requires two consecutive injection cycles to optimize effect.

IPD participants will complete all visits in their optimal “on” state relative to their PD medications. Participants will be asked to take other medications as normal. They will be instructed not to ingest caffeine on the day of assessment to minimize confounding of tremor data. For all participants, the tremor dominant hand will be targeted for injection.

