Xeomin® will be re-constituted by the same clinical nurse for all injections. This is done to ensure methodological consistency. To reduce bias, a single MDN will complete all injections for both groups. The MDN will determine parameters of injection using kinematic data for each injection course. The injecting MDN will be blinded to the kinematic/video recordings, but will make decisions from the analyzed data. Needle EMG may be utilized at the discretion of the MDN to ensure accuracy of injection sites in accordance with routine clinical practice. The injecting MDN will receive training in interpreting of kinematic data results prior to the initiation of the study.

*Duration:* Participants will receive a total of 6 injections and attend 13 study sessions over the course of 96 weeks. Duration of each participant visit will be approximately 75-90 minutes.

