## **Dosage Regimen**

100-300 units injected intramuscularly every 16 weeks.

*Rationale:* In clinic, injections are given every 12 weeks. To ensure complete wearing-off of drug effects before re-injection and prevent possible excess weakness, we have extended this period by 4 weeks.

*Drug Schedule:* Any changes to injection dosing or parameters will be based on kinematic measurements, though injection parameters will also be influenced by clinical outcome measures, as is the current standard clinical practice for Xeomin® injections.

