## Statistical Analysis

Flow charts for description of statistical method by research question follow. Alpha level set at 0.05 for all analyses. Statistical method assumes that criteria will be met for parametric statistics.

*Primary endpoint - Research Question 1:* Is there a significant improvement in tremor severity as measured by standardized clinical assessment tools post Xeomin® injection using kinematic guided injection parameters for both IPD and ET?

[figure not shown]

Repeated measures ANCOVA was selected to reduce variance associated with baseline variability in tremor severity. This is important for the design given that there is classically significant variability of tremor at baseline making it unrealistic to achieve a rigorously matched sample across all relevant variables.

*Secondary endpoint*) - Research Question 2: Is there a significant reduction in overall tremor amplitude post Xeomin® injection using kinematic guided injection parameters for both IPD and ET?

[figure not shown]

*Not a clinical endpoint* - Research Question 3: What is the difference in composition of tremor at baseline between two subgroups of participants: those with > 8 points change and those with ≤ 8 points change on standardized tremor clinical rating scales?

[figure not shown]

Supplement: S1 File — (PDF) [file pone.0178670.s001.pdf]

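### Objective 2, the benefit of kinematic tools for setting injection parameters, cannot be answered because every injection uses kinematic data and nothing is compared with clinical-only guidance

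*Protocol*

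**What the plan says.** Trial Objectives lists three aims. The first is efficacy of injections based on kinematic parameters and the third is tremor composition. The second is to "Assess the benefit of using kinematic measurement tools for determining BoNT A injection parameters".

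The protocol then fixes how injections are chosen:

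- **Study Design and Duration:** the design is open-label and pre/post, with one treatment approach for everyone. "The MDN will determine parameters of injection using kinematic data for each injection course". The neurologist "will be blinded to the kinematic/video recordings, but will make decisions from the analyzed data".
- **Same section, later cycles:** "Clinically judged improvement (by the MDN) and patient reported improvement will be the determinants of need for dose/injection site modification". Also, "If the first injection was sufficient in reducing tremor to an acceptable level, the same injection will be repeated".
- **Dosage Regimen:** changes rest on kinematic measurements, "though injection parameters will also be influenced by clinical outcome measures, as is the current standard clinical practice".
- **Research questions:** question i asks about clinical improvement under kinematic guidance. Question ii reads "Is there a significant reduction in overall tremor amplitude (as measured kinematically) post Xeomin® injection using kinematic guided injection parameters", for both diagnoses. Question iii compares baseline tremor composition between participants above and at or below an 8-point change.
- **Statistical Analysis:** "Flow charts for description of statistical method by research question follow", and the questions listed there are the same three.

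**The concern.** Objective 2 is comparative in substance: whether choosing muscles and units with kinematic data is better than choosing them without. Nothing in the protocol provides the second half of that comparison. No research question maps to the objective either.

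The background section on kinematic versus clinical assessment presents parameter-setting from kinematic data as under-researched and as a gap this project attempts to fill. Readers will therefore look for an answer. The only result available is an uncontrolled pre/post change, which is easily misread as showing that the guidance worked. That change mixes the toxin effect, open-label expectation, regression to the mean and repeated dose adjustment with any contribution of the guidance.

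**Working it through.** **1. The plan's own calculation (Sample Size).** Inputs: two-sided alpha 0.05, effect size 0.44, N = 70 as 35 + 35. Taking 0.44 as Cohen's f in a two-group ANCOVA with one covariate, the noncentrality is f² x N = 0.44² x 70 = 13.55.

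| N | Attrition | Critical F | Power |
|---|---|---|---|
| 70 | none | 3.98 | 0.952 |
| 56 | 20% | 4.02 | 0.898 |
| 44 | 37% | 4.08 | 0.813 |

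These match the stated figures. They do not concern objective 2, because the only groups in the design are the two diagnoses.

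**2. Is there a comparator for kinematic guidance?**

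| Possible source | What the protocol provides |
|---|---|
| Parallel arm | None; groups are IPD and ET |
| Clinical-only cycle within a participant | None; kinematic data are used for each course |
| Recorded clinical-only plan | None |
| Historical comparison | None |
| Research question | None of i to iii |

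Planned injections: 70 x 6 = 420. Number with parameters set without kinematic data: 0. Attrition lowers the 420 and leaves the 0.

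The clinical and patient-reported input to later cycles does not create a contrast. It applies to everyone, and an injection that worked is repeated with parameters first set from kinematic data.

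**3. Consequence for interpretation.** Write the mean pre/post change as (everything else) + (guidance contribution). With one regimen only the sum is observed: 8 = 8 + 0 and 8 = 0 + 8 fit equally well.

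**4. What a comparison of outcomes would need (illustration).** The protocol gives no effect size for this contrast. Using the same ANCOVA at 80% power and dividing by 0.7 for the expected 30% attrition:

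| Assumed f | Evaluable | Recruited |
|---|---|---|
| 0.44 | 43 | 62 |
| 0.33 | 75 | 108 |
| 0.22 | 165 | 236 |

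**5. What a descriptive objective could deliver.** For the share of plans changed by kinematic data, the widest 95% half-width is 1.96 x √(0.25/n):

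| n | Basis | Half-width (points) |
|---|---|---|
| 70 | all participants | 11.7 |
| 49 | 70 x 0.70, completers | 14.0 |
| 35 | one diagnosis | 16.6 |
| 24 | one diagnosis, completers (35 x 0.70 = 24.5, rounded down) | 20.0 |

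Wilson 95% intervals at n = 70 are 20.5% to 41.5% for 21 changed plans and 38.6% to 61.4% for 35. If none of 70 changes, the exact two-sided 95% upper limit is 1 − 0.025^(1/70) = 5.1%.

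For the mean change in units, the 95% half-width is t/√n standard deviations: 0.24 SD at n = 70 and 0.29 SD at n = 49. The SD is not given. Assuming 20, 40 or 60 units, the half-width is 4.8, 9.5 or 14.3 units at n = 70 and 5.7, 11.5 or 17.2 units at n = 49.

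**The case against.** **A non-comparative reading.** Objective 2 names no comparator. It could mean only whether patients benefit when injections are set this way, which questions i and ii address, in a study that calls itself a pilot. But that reading makes objective 2 a repeat of objective 1, which already covers efficacy of injections based on kinematic parameters. Pilot status may excuse the lack of a control group. It does not make the objective answerable.

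**The background describes development.** It also speaks of developing recording methods, analysis methods and clinical expertise, and the protocol nowhere says that pre/post change will be credited to guidance. This is fair, and it limits the harm to misinterpretation. It is also a reason to word the objective as description.

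**The flow charts and the SAP were not available.** True, but the questions printed with the charts contain no guidance contrast, and no analysis can create a comparator that was never collected.

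**How far kinematic data drive later cycles is unclear.** This stands. It makes the contribution of kinematic data harder still to isolate and leaves the comparator at zero.

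**Limits of the remedy.** It covers injection 1 only and measures changed plans, not patient benefit. One neurologist writes both plans knowing that kinematic data will follow. All of this stands. The protocol also does not say when the neurologist examines the patient relative to receiving the analysed data, so that order must be written in.

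**Conclusion.** The concern holds. Objective 2 asks about a benefit that the design cannot estimate: 0 of 420 planned injections are set without kinematic data, at any level of attrition. The reasons given for having no control group cover injecting people without tremor and comparing two formulations; a clinically guided comparator is not considered.

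The conclusion rests on reading objective 2 as distinct from objective 1 and on taking at face value the statement that kinematic data are used for each course. The primary and secondary endpoints, question iii and the sample size are untouched. The change should be made, but it does not threaten the rest of the study.

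**What to change.** 1. Reword objective 2: *Describe how often, and by how much, analysed kinematic data change the muscles and units that the neurologist would choose from clinical examination alone.*
2. Before injection 1, the neurologist records muscles and units from clinical examination, then sees the analysed kinematic data and records the final plan. The protocol should fix this order. It is compatible with the existing schedule: a neurologist assesses participants for allocation, Pre-Study Screening and Baseline Evaluation places no kinematic assessment before the first study visit, and the injecting neurologist works only from analysed data.
3. Define a changed plan in advance, for example any muscle added or dropped, or a stated change in total units.
4. Report the share of plans changed and the mean change in units and muscles, with 95% confidence intervals, overall and by diagnosis.
5. Add: *Pre/post results will not be interpreted as evidence that kinematic guidance is better than clinical guidance.*

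The cost is one extra record per participant, a reworded objective and one added sentence. No extra participants or visits are needed and treatment is unchanged. The price is a more modest objective: it shows whether kinematic data alter plans, not whether patients do better. If the extra record is unwelcome, a purely descriptive rewording of objective 2 (how kinematic data are used to set injections) with step 5 would still remove the unanswerable claim.

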## *Research questions:*

- i. Is there a significant improvement in tremor severity, as measured by standardized clinical assessment tools, post Xeomin® injection using kinematic guided injection parameters, for both IPD and ET patients?
- ii. Is there a significant reduction in overall tremor amplitude (as measured kinematically) post Xeomin® injection using kinematic guided injection parameters for both IPD and ET?
- iii. What is the difference in composition of tremor at baseline between two subgroups of participants: those with > 8 points change on the standard Fahn-Tolosa-Marin Tremor Rating Scale (FTM scale) and those with ≤ 8 points change the FTM scale?

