### **Sample Size**

*Number of subjects:* 70

*Sample size justification:*

|             |                               |
|-------------|-------------------------------|
| Alpha error | Alpha error = .05, two-sided. |
|-------------|-------------------------------|

|                                                  |                   |
|--------------------------------------------------|-------------------|
| Statistical power                                | $1-\beta = 0.95$  |
| Difference detectable with specified sample size | Effect size = .44 |

*Sample size calculations:* Power calculations are based on our previous pilot study as well as a review of relevant literature. We have based all power calculations at  $1-\beta = .95$  to ensure efficacy for the primary endpoint. Power calculations were conservatively based on *F*-test paradigm for ANCOVA using G\*Power 3.1.2 software package. Alpha error = .05.

There were no relevant studies on Xeomin® and hand tremor found in the literature search. To calculate effect size for efficacy of hand tremor management using Botulinum toxin A, we have used a randomized, double masked study of efficacy in essential tremor by Brin, et al. (2001). They calculated the effect size for  $N = 133$  (allocated to two groups high (100 units) and low (50 units)). For the current power calculation the low unit group was used as a conservative estimate. For tremor scale measures (primary endpoint) we used an effect size = .44 (Brin, et al. 2001). Based on previous studies in our group, we would anticipate a lower effect size for the kinematic outcome measures (secondary endpoint) estimated at .33 (overall tremor amplitude).

The target sample size for this study is  $N = 70$  (35 per group for both IPD and ET), which will allow for  $1-\beta = .95$  for an effect size for the primary endpoint of .44 and critical  $F = 3.98$ . This sample size will allow for an attrition rate of 20% while maintaining a  $1-\beta = .90$  ( $F = 4.02$ ) and an attrition rate of 37% while maintaining  $1-\beta = .80$  ( $F = 4.08$ ). Given the length of the study (5 visits over 8 months) we estimate a 30% attrition rate and have planned conservatively for that.

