## Efficacy Variables and Analysis

*Clinical efficacy variables (primary endpoint):* Improvement in hand tremor as determined by a decrease  $> 8$  points on a standardized clinical assessment tool (Fahn-Tolosa-Marin Tremor Rating Scale) post-Xeomin® injection. A point change of 8 points was selected based on studies of oral tremor medications showing mean improvement ranging from 7.5 to 10 points increase on the same clinical scale, which statistically produced moderate-large effect sizes.

*Kinematic efficacy variables (secondary endpoint):* Improvement in hand tremor measured as a 50% reduction in overall tremor amplitude post-Xeomin® injection.

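### Research question 3 splits the FTM change score at 8 points when the full scale is available; the split costs information, by an amount the protocol's figures cannot fix

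*Protocol*

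**What the plan says.** The protocol's Research questions section, item iii, compares tremor composition at baseline between "those with > 8 points change on the standard Fahn-Tolosa-Marin Tremor Rating Scale (FTM scale) and those with ≤ 8 points change the FTM scale". The Statistical Analysis section repeats the question with the same cut-point: "What is the difference in composition of tremor at baseline between two subgroups of participants: those with > 8 points change and those with ≤" (the quotation breaks off just before the cut-point). There the question is marked as not being a clinical endpoint, and the flow chart giving its method is not reproduced in the text at hand.

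The 8-point mark comes from Efficacy Variables and Analysis, where a decrease of more than 8 points defines improvement on the primary endpoint. The reason given is: "A point change of 8 points was selected based on studies of oral tremor medications showing mean improvement ranging from 7.5 to 10 points". On error rate the protocol says "Alpha level set at 0.05 for all analyses", and the Sample Size section has "Alpha error = .05, two-sided".

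The Sample Size section sets power "to ensure efficacy for the primary endpoint". It gives a total of 70 participants and an expected attrition of 30%. It states no power, effect size or responder share for research question 3.

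**The concern.** The split treats a participant who improves by 9 points as the opposite of one who improves by 8, and as the same as one who improves by 25. The argument for 8 points is a benchmark for calling a clinical change an improvement. It does not show that response has two states, and it gives no reason to cut the score when the aim is to learn which tremor components go with response.

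This is the only one of the three research questions that relates tremor composition to response. It has at most 70 participants, or 70 × 0.70 = 49 after the stated attrition. Discarding information in a sample of that size makes a real association easier to miss.

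**Working it through.** **1. The protocol's own power figure.** It belongs to the primary endpoint: "For tremor scale measures (primary endpoint) we used an effect size = .44". Taking .44 as Cohen's f in a noncentral F test with 1 numerator degree of freedom and λ = f²N:

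- N = 70: λ = 0.1936 × 70 = 13.55, critical F = 3.98, power 0.952 (stated: 3.98, .95).
- N = 56 (20% attrition): λ = 10.84, critical F = 4.02, power 0.898 (stated: 4.02, .90).
- N = 44 (37% attrition): λ = 8.52, critical F = 4.08, power 0.813 (stated: 4.08, .80).

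These figures reproduce, but they say nothing about research question 3.

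**2. Information kept after a split.** If a normal variable is cut so that a share p lies above the cut c = z(1 − p), the relative efficiency is φ(c)² / [p(1 − p)].

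- p = 0.5: 0.3989² / 0.25 = 0.637 (that is, 2/π), a loss of 36%.
- 40/60: loss 38%. 30/70: 42%. 20/80: 51%. 10/90: 66%.

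The even split is the best case, so 36% is a floor under normality.

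**3. Where 8 points might fall.** The protocol quotes mean changes of 7.5 to 10 points for oral drugs and no standard deviation. I assume a standardised effect of 0.5 to 0.8.

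- Mean 7.5: SD = 7.5/0.5 = 15 or 7.5/0.8 = 9.4; share above 8 is 49% or 48%.
- Mean 10: SD = 20 or 12.5; share above 8 is 54% or 56%.

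The loss is then 36 to 37%. This supposes that injected toxin produces changes like those of oral drugs, which the protocol does not claim.

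**4. Power.** The check simulates bivariate normal data with one composition measure, a two-sided alpha of 0.05 and an even split. It compares a correlation test on the full scale with a two-sample t-test after the cut.

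| N | Assumed correlation | Full scale | Split | Points lost |
|---|---|---|---|---|
| 70 | .30 | 0.72 | 0.53 | 19 |
| 70 | .40 | 0.94 | 0.78 | 16 |
| 49 | .30 | 0.56 | 0.39 | 17 |
| 49 | .40 | 0.83 | 0.62 | 21 |

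Repeat runs move these values by about a point.

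**5. Sensitivity.** At N = 70 with an even split the loss is 12 points at a correlation of .2 and 5 points at .5. Over correlations of .2 to .5, 20 to 50% responders and both sample sizes, it ranges from about 5 to 32 points. The full-scale analysis had the higher power in every setting tried.

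**The case against.** The strongest defence is coherence. The protocol defines improvement as a decrease of more than 8 points, and research question 3 asks how those who meet that definition differed at baseline from those who did not. Using one threshold throughout is consistent. It does not follow that the split must carry the inference: a descriptive display by responder status keeps the link to the endpoint.

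Second, the size depends on inputs that the protocol does not supply. This stands. A reader might infer that the split costs a fixed 15 to 20 points of power. The documents do not support that, because they give no SD, responder share or correlation for this question. Nor can the effect sizes .44 and .33 stand in for that correlation: they are for tremor scale measures and overall tremor amplitude, not for an association between composition and response.

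Third, the simulation uses one measure, while composition has several parts. Treatment / Assessment Visits describes six degrees of freedom (three at the wrist, one at the elbow, two at the shoulder). With five free predictors, one of them carrying the signal, and an even split, power at N = 49 and a correlation of .30 was 0.30 against 0.19. The loss persists, but the absolute powers tabulated above do not describe a joint test.

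Fourth, the flow chart is not visible, so the t-test comparator is an assumption and an accompanying continuous analysis cannot be excluded. The wording of the question in both sections nevertheless fixes the two-subgroup comparison.

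Finally, this is an exploratory question in a pilot, with no power claim. That limits the weight of the point but does not remove it.

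**Conclusion.** The point holds in conditional form. Research question 3 reduces to two groups a score that is available in full, and the stated reason for 8 points covers only the clinical endpoint. Under normality at least 36% of the information is lost. The 15 to 20 point fall in power requires one composition measure, a near-even split and a correlation of about .3 to .4; the wider range is about 5 to 32 points.

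A reader might go further and infer that the efficacy analysis is compromised. The documents do not support that: the question is marked as outside the clinical endpoints, and the sample size was not justified on it.

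**What to change.** In Research questions (iii) and in the matching paragraph of Statistical Analysis, restate the question as how baseline tremor composition relates to FTM change. Analyse FTM change as a continuous outcome by regression on the composition measures, with diagnosis group (IPD or ET) as a covariate so that the two populations are not simply pooled. If composition is expressed as shares of amplitude, the shares sum to one and cannot all enter with an intercept. Omit one share as reference, or use the component amplitudes themselves. Keep the comparison above and at or below 8 points as a descriptive display.

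The cost is the rewording of one question and its analysis. No new data, visits or participants are needed. The result becomes a slope instead of a two-group difference, and the display still shows the latter.
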